#### Sample size

##### a) Definite cases

150 participants with a GHQ score >5 will be recruited from each of 24 facilities. Based on the piloting stage experience that up to 25% of these participants will either not be traced by the outcome evaluators or will not consent to participate, and that at least 1 in 3 'cases' identified by the GHQ are Sub-Threshold cases, we anticipate that at least 75 definite cases (see Table 3) from each facility will complete the outcome evaluation at the 6 month end-point. This gives a total sample size of 1800 in which to assess our primary outcome: recovery rate of ICD-10 defined CMD at 6 months among definite cases at baseline. This will have more than 90% power to detect at the 5% level of significance a difference in recovery rates of 70% in the Collaborative Stepped Care versus 50% in the Enhanced usual care control arm. If the recovery rates are 65% and 50% respectively, we will have 74% power to detect a significant difference. Similarly, we have around 90% power to detect a difference in proportion recovered from depression at 6 months of 50% in the Collaborative Stepped Care arm versus 30% in the Enhanced usual care arm.

The assumptions underlying this calculation are as follows. The recovery rates in the Chilean trial [18], whose intervention model is the one being used in this study, showed a gap in recovery at 6 months of 70% versus 30% between the two groups. However, our trial is evaluating effectiveness of introducing this model into routine care, and so we would expect a smaller difference between rates than in an efficacy trial. Furthermore the Chilean trial focused on Depression, while ours will also recruit subjects with less severe CMD who might potentially have higher spontaneous recovery rates in both treatment arms. There are no existing data on the recovery rates of CMD in routine PHC or GP in India. The limited data from other developing countries, including outcomes of Usual Care groups in efficacy trials, suggests that between 30% and 50% of subjects with a CMD recover without active intervention by 6 or 12 months after recruitment [16,18,58]. We therefore based our primary sample size calculation on a likely conservative difference of 20% between the two arms (compared to 40% in the Chile trial), and on recovery rates of 30–50% in the Enhanced usual care control arm.

A key factor in estimation of the sample size for a cluster RCT is the coefficient of variation (SD/mean) of the true proportions with the outcome between clusters within each arm [59]. In the absence of outcome data to estimate k in Goa, we have used the recovery rates of CMD in the two Asian centres (Shanghai, Bangalore) of the WHO multinational study of CMD in general health care [10], and data from 8 studies of CMD prevalence in India (two in urban GPs, three in urban PHCs and three in rural PHCs) [12] all of which estimate k < 0.2. The proposed trial is located in one state of India and facilities are stratified according to their rural/urban location and private/public sector; hence the value of k is likely to be even lower [59,60]. To be conservative, we have used an estimate of k = 0.2.

##### b) Possible cases

We expect about one-third of possible cases to be sub-threshold cases at baseline, as defined by the CIS-R, and that 10% of these might become new cases in the EUC arm compared to 5% in the CSC arm. In addition, we assume that 50% of the definite cases at baseline will still be cases at 6 months in the control arm, compared to 30% in the intervention arm. So overall, we will expect prevalence of CMD at 6 months amongst possible cases at baseline to be 37% in the control arm (10% × 1/3^rd ^+ 50% × 2/3^rd^), and 22% in the intervention arm (5% × 1/3^rd ^+ 50% × 2/3^rd^). We will have 99% power to detect this difference at the 5% significance level, assuming a 75% follow-up rate as above.

A secondary outcome in this group is the mean CIS-R score at 6-months among probable, i.e. screen-positive, cases at baseline. Our earlier longitudinal study of confirmed ICD10 cases at baseline found a reduction in mean CISR score of 50% over 6 months from 24 (s.d. 6) to 12 (s.d. 10) [16]. We would expect slightly lower CISR scores among all possible cases at baseline in our study. Our sample size gives high power (100%) to detect a difference in CIS-R score at 6 months of 18 (s.d. 10) in the Enhanced usual care control arm versus a CIS-R score of 9 (s.d. 10) in the Collaborative Stepped Care arm.

##### c) Sub-threshold cases

The only cohort study of primary care attenders which has reported on risk factors for new cases of CMD from a developing country was carried out in Zimbabwe [61]; in this study, the proportion of sub-threshold cases at baseline who became cases at 6 months was 31% (19 out of 61 subjects). Assuming a 75% follow-up rate we will have an effective sample size of 900 sub-threshold cases; this gives about 70% power to detect a difference in the proportion with CMD at 6 month follow-up between 5% in the intervention arm and 10% in the control arm.

##### d) Depression cases

Our pilot data has shown that only 1/3 of CMD cases are suffering from ICD-10 depression. Thus the proposed sample size would yield about 25 depression cases per facility traced at 6 months, giving a total effective sample size of 600; this has 94% power to detect a difference in recovery rates of 30% in the Enhanced usual care control arm and 50% in the Collaborative Stepped Care arm at 6 months. Again these are conservative estimates compared to the achievements of the Chile trial.

##### e) Cost effectiveness

We have not powered our trial for the cost-effectiveness outcome because we expect the intervention to be dominant as compared to the usual care, i.e. improved outcomes *and *lower costs. Thus, additional resources required to implement the intervention are expected to be fully or partially offset by reduced consumption and associated costs of other health care services (especially outpatient attendance for somatic symptoms) and to also lead to reduced opportunity costs to patients and families (especially lost work days). This is what we found for the antidepressant arm in the earlier cost-effectiveness trial in Goa [16].

### Data management & analyses

Data will be collected using a hand-held computer (Palm-OS), and exported to Stata 9.0 for statistical analysis. Given direct entry of responses, we expect there to be minimal data entry errors. Findings will be reported as per the CONSORT guidelines for cluster randomized controlled trials [62]. Baseline comparability will be assessed for individuals who did not consent to be part of the trial, and of participants who could and could not complete review assessments. Comparability of the two intervention arms will be assessed for a variety of potential confounding factors assessed at 2 months, notably: age, sex, education, per capita income, severity of mental health scores, ICD10 diagnostic distribution, and comorbidity with alcohol use and physical health problems.

The primary analyses will be intention-to-treat, regardless of adherence to the intervention, and will be based on outcomes 6 months after diagnosis. Logistic regression generalized estimating equations with robust standard errors will be used to compare case prevalence in the two arms, allowing for any within-facility clustering resulting from the cluster randomized design [63], and adjusting for baseline mental health score. Further analyses will adjust for any other of the a-priori defined confounding factors list above for which randomization did not achieve balance between the two arms at baseline. These analyses will be carried out for the different patient groups defined in Table 3, with their respective outcomes as described above. For each of these primary outcome analyses, we will present an estimate of the effect size as an odds ratio and 95% confidence intervals, and a coefficient of intracluster correlation. A number of secondary analyses are proposed, which are listed in the Trial Registration protocol.

For the economic analysis, health care costs and other patient- or family-borne costs will be computed and compared at 2, 6 and 12 months, and subsequently related to changes in health outcome: both the primary outcome measure of depression status and also Quality Adjusted Life Years (QALYs). A culturally specific and conceptually solid utility measure for depression – necessary for the estimation of QALYs – will be generated by relating health state valuation scores (taken from an Indian population as part of a wider WHO multi-country study) to summary scores on the WHO-DAS. In the event that dominance is not shown, i.e. the intervention is more effective but the costs are also more than the usual care group, we will estimate the probability of dominance and estimate incremental net benefit and incremental cost-effectiveness ratios. The latter will be computed, together with their confidence intervals (using bootstrapping techniques to overcome expected skewness of cost data). Cost-effectiveness acceptability curves will also be derived in order to show the probability of any cost-effective advantages for the component interventions at a range of 'willingness to pay' threshold levels.

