### Trial objectives and outcomes

It is our objective to study the overall effect of the intervention on the treatment and outcome of CMD in primary care. Four primary research questions are being addressed in the trial, relating to clinical outcomes in different groups of patients, defined according to their type of CMD at baseline (Table 2). From a practical or policy perspective, we need to evaluate the impact on all patients who are identified on the basis of the short screening procedure. Our primary analysis will focus on the subgroup for whom previous evidence is clearest regarding benefit: definite ICD-10 CMD. The outcome will be assessed through home visits at 6 months using the CISR which generates both CMD case and Depression case outcomes based on ICD10 criteria; and a CISR total score. Six months is chosen as the primary endpoint because it marks the maximum duration of the first-line drug and psychological components of the intervention. Other end-points at 2 and 12 months will assess the rate and persistence of clinical recovery. Other outcomes include recovery from Depression, the mean CIS-R score, and prevalence of ICD-10 among sub-threshold cases (Table 2).

In addition, economic costs and outcomes will be measured using the Costs of Illness Schedule, developed for economic analyses of mental disorders in India [9] and used in the previous efficacy trial in Goa [16]. This schedule includes both direct and indirect costs, due to health problems, incurred by the participants, but does not include the direct costs of the intervention itself. The latter will be computed by deriving a monetary value for each component of the intervention based on actual costs, and applying these to each individual based on the process indicators which reflect the actual contact with the intervention. Disability levels will be assessed using the WHO12 item Disability Assessment Schedule, based on the Brief Disability Questionnaire which has been used in Goa [14,57], and input into the estimation of opportunity costs.

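### The arm-comparability check uses confounders dated to 2 months, after treatment has started, and conflicts with the baseline date in the rule for the further adjusted analyses

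*Protocol article*

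**What the plan says.** All of the analysis text is in the protocol article, section Data management & analyses.

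- **Comparability check.** "Comparability of the two intervention arms will be assessed for a variety of potential confounding factors assessed at 2 months". The named factors are age, sex, education, per capita income, and then "severity of mental health scores, ICD10 diagnostic distribution, and comorbidity with alcohol use and physical health problems".
- **Primary model.** Logistic regression by generalised estimating equations on 6-month outcomes, "adjusting for baseline mental health score".
- **Supplementary models.** "Further analyses will adjust for any other of the a-priori defined confounding factors list above for which randomization did not achieve balance"; the sentence ends by placing that balance at baseline ("balance between the two arms at baseline").

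Three other places fix what 2 months means in this trial:

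- Table 1 (steps of the collaborative stepped care intervention) puts Step 1 at the first consultation, and Step 2 there too for the severely ill.
- Trial objectives and outcomes: "Other end-points at 2 and 12 months will assess the rate and persistence of clinical recovery".
- Selection of study participants has the CIS-R done at enrolment, after a positive GHQ. Severity and ICD-10 diagnosis therefore exist from that point.

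**The concern.** A comparability check asks whether randomising 24 facilities, and recruiting within them, produced similar patients in the two arms. Only values that treatment could not have changed can answer that. Age, sex and education qualify whenever they are asked. Severity and diagnosis at 2 months do not. They are early readings of the outcome, and an intervention that works quickly will make them differ between arms.

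Two things are at stake. First, a 2-month comparison could show a difference where the arms started alike, or hide one where they did not. It would also cover only patients traced and consenting at that visit, which Ethical considerations gives as the outcome team's first home visit. Second, if 2-month diagnosis or severity entered the further models, the arm coefficient would no longer carry the benefit that had already appeared by 2 months and persisted. Those models are the natural robustness check on the primary result, so a weakened estimate could be misread as evidence that confounding explains the effect.

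**Working it through.** **1. The two sentences side by side**

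| Item | Comparability sentence | Adjustment sentence |
|---|---|---|
| Factors | the listed confounders | the same list |
| Date | assessed at 2 months | balance at baseline |
| Use | judge whether arms are comparable | choose covariates for further models |

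For time-fixed items the two dates agree. For severity and diagnosis they do not, because treatment and an outcome assessment fall between them. For alcohol use, physical comorbidity and income, an effect of treatment by 2 months is possible but less certain.

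**2. The plan's own scenario**

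The Sample size section gives 70% v 50% recovery, 75 definite cases per facility, 24 facilities (12 per arm) and k = 0.2. With variance v = p0(1−p0)/m + p1(1−p1)/m + k²(p0² + p1²):

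- 70% v 50%: v = 0.00333 + 0.00280 + 0.0296 = 0.03573; √(11 × 0.20²/0.03573) = 3.51. With t on 22 df, power is 91.7% (stated: above 90%).
- 65% v 50%: v = 0.00333 + 0.00303 + 0.0269 = 0.03327; √(11 × 0.15²/0.03327) = 2.73. Power is 74.0% (stated: 74%).

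The stated power reproduces, and the timing problem does not change it. The scenario is used below only as the size of the true effect.

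**3. What adjustment for 2-month values would do (illustrative)**

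Assumptions, none of them in the documents:

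- Severity is normal with unit SD within arm, and clustering is ignored.
- The correlation between baseline and 2-month severity is 0.5.
- Carry-over r from 2-month to 6-month severity is 0.4 or 0.6.
- A fraction f of the eventual effect is already present at 2 months.

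With A = 1 for the intervention arm and D = Φ⁻¹(0.70) − Φ⁻¹(0.50) = 0.524:

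- S2 = 0.5·B − f·D·A + error
- S6 = r·S2 − (1 − r·f)·D·A + error; recovered if S6 < 0

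The total effect on S6 is D whatever f is, so recovery stays at 70% v 50%. Given S2, the arm effect left is (1 − r·f)·D on a residual SD of √(1 − r²). Multiplying by about 1.65 converts this to a log odds ratio.

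| Case | r = 0.4 | r = 0.6 |
|---|---|---|
| Half present (f = 0.5) | 0.8 × 0.524/0.917 = 0.457; OR 2.13 | 0.7 × 0.524/0.8 = 0.459; OR 2.13 |
| All present (f = 1) | 0.6 × 0.524/0.917 = 0.343; OR 1.76 | 0.4 × 0.524/0.8 = 0.262; OR 1.54 |

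Simulating the same model (one million patients per setting) gives:

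| Covariates | Half present | All present |
|---|---|---|
| Baseline severity only | about 2.4 | about 2.4 |
| + 2-month severity | about 2.15 | about 1.55–1.75 |
| + binary 2-month diagnosis only | about 2.25–2.3 | about 1.9–2.0 |

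The binary diagnosis was set so that half of control patients are non-cases at 2 months.

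**4. Sensitivity to the model**

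A variant lets baseline severity also act directly on 6-month severity, with carry-over from 0.3 to 0.7. There, adding 2-month severity cuts the standardised 20-point difference to about 13–17 points if half the effect is present at 2 months, and to about 6–14 points if all of it is. With no effect by 2 months the difference stays at 20 points. The risk difference is the cleaner scale: adding any strong predictor raises a conditional odds ratio, which can mask part of the loss.

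**The case against.** The strongest reply has four parts.

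**The primary result is safe.** A reader might infer that the trial's main odds ratio is biased. The documents do not support that: the primary model adjusts for the baseline score, and the listed factors enter only in further analyses. This stands in full.

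**The trigger names baseline.** A reader might also infer that the plan commits to adjusting for differences that treatment itself has produced. Taken literally, the adjustment rule excludes them, since a treatment-made difference at 2 months is neither a failure of randomisation nor a baseline imbalance. This stands too, and it makes the defect a contradiction rather than a declared plan to adjust for mediators. It does not remove the defect. The only dated description of the listed factors says 2 months, so an analyst following it would hold 2-month values when applying the rule.

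**Severity is the item least likely to be added.** The rule covers other factors beyond the baseline score already in the model. Diagnosis and comorbidity are therefore more exposed, and the smaller losses in the diagnosis row are the more relevant ones.

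**The authors may have meant background items first collected at the 2-month home visit.** That is plausible and harmless for age, sex and education. It does not cover severity and diagnosis, which change over time and were already measured at enrolment.

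**Conclusion.** The point holds in a limited form. The comparability sentence gives the wrong date for every changeable item on its list and contradicts the adjustment rule that follows. The harm falls on the arm-comparability check and the supplementary adjusted analyses.

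If 2-month severity or diagnosis were used, the adjusted effect would be pulled toward no effect to the extent that the intervention works early and the benefit lasts. The direction is firm on the risk-difference scale. The size rests on assumed carry-over and timing, so the odds ratios above show the order of magnitude and are not predictions.

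Much larger attenuation, to odds ratios of 1.25–1.33, arises only if three quarters of the 6-month effect runs through 2-month severity. With carry-over of 0.4–0.6, that needs a 2-month effect of 0.75/0.6 = 1.25 to 0.75/0.4 = 1.9 times the 6-month effect. Nothing in the protocol supports assuming this.

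Choosing covariates by observed imbalance is a separate and lesser weakness, and the conclusion does not depend on it.

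**What to change.** In Data management & analyses:

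1. Define both the comparability check and the adjustment set on values at enrolment, using the GHQ score, the CIS-R score and the ICD-10 diagnosis obtained then.
2. Allow the 2-month visit as a source only for time-fixed items such as age, sex and education.
3. State that severity, diagnosis and comorbidity measured at 2 months will not be used as covariates for the 6-month outcome.
4. Reconcile the two sentences so that the list and the rule carry the same date.

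For severity and diagnosis this is a change of wording, since the data are already collected. For income, alcohol use and physical comorbidity the cost is less certain: the article documents only the GHQ and CIS-R at enrolment. If those items are first recorded at 2 months, they drop out of the adjustment set. That is a small loss, because the primary model does not use them.

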### Study design

The stepped care model will be evaluated using a cluster-randomized trial which will be implemented in two consecutive phases over 2 1/2 years beginning in April 2007. Phase 1 involves 12 public facilities (Primary Health Centres or PHCs), 6 of which have been chosen at random to deliver the stepped care model to patients screened positive for CMD with the other 6 "control" facilities delivering enhanced usual care control. Phase 2 will be conducted in 12 private facilities (General Practitioners or GPs).

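### The primary GEE on 24 facilities names no small-sample correction and omits the randomisation strata, so its type I error is not held at 5% and could err in either direction

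*Protocol article*

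**What the plan says.** The analysis section (Data management & analyses) names the estimator and the variance method: "Logistic regression generalized estimating equations with robust standard errors will be used to compare case prevalence in the two arms". The model allows for clustering by facility, "and adjusting for baseline mental health score". Other covariates come later and only if imbalanced: "Further analyses will adjust for any other of the a-priori defined confounding factors list above". That list holds patient characteristics; the randomisation strata are not on it. The same model is to be used for the different patient groups, with odds ratios and 95% confidence intervals.

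The number of independent units is small. Under Sample size, a) Definite cases: "150 participants with a GHQ score >5 will be recruited from each of 24 facilities", and "we anticipate that at least 75 definite cases (see Table 3) from each facility will complete the outcome evaluation". Allocation was stratified. Selection of facilities/randomisation describes three strata in phase 1, with two intervention and two control centres drawn from each, and says phase 2 will be stratified in a similar way. The sample size section assumes a between-cluster coefficient of variation of k = 0.2 and expects stratification to bring it lower.

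**The concern.** The robust (sandwich) variance is justified when the number of clusters is large. With 12 facilities per arm it is biased downward, and a normal reference ignores the fact that the variance is estimated from few units. That pushes the test towards rejecting too often.

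Stratification works the other way. If strata account for some of the facility variation, balanced allocation within strata makes the treatment contrast more precise. A model without strata does not see that gain, so its standard error is too large.

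The stated analysis carries both faults, and their net effect depends on something unknown at the planning stage. At stake are the size of the primary test and the coverage of its interval, and the same for the other patient groups analysed this way.

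**Working it through.** **Inputs.** From the protocol: 24 facilities, 12 per arm; 75 definite cases per facility; k = 0.2, an SD of 0.10 at a recovery rate of 50%; significance "at the 5% level of significance". Assumed: two-sided test; exchangeable working correlation; six strata of four facilities (three stated for phase 1, three more taken for phase 2); a baseline-score effect of 0.5 on the logit scale per SD.

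**Step 1: reproduce the stated powers.** With c clusters per arm, m per cluster and an allowance of a clusters per arm:

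power = Φ( √[(c − a)(p0 − p1)² / V] − 1.96 ), where V = p0(1 − p0)/m + p1(1 − p1)/m + k²(p0² + p1²).

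For 65% v 50%, m = 75: V = 0.25/75 + 0.2275/75 + 0.04(0.25 + 0.4225) = 0.0333. With a = 2, √(10 × 0.0225/0.0333) = 2.60, and Φ(0.64) = 73.9%.

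| Scenario | Stated | a = 0 | a = 1 | a = 2 |
|---|---|---|---|---|
| 65% v 50%, m = 75 | 74% | 81.3% | 77.9% | 73.9% |
| 70% v 50%, m = 75 | >90% | 95.6% | 93.9% | 91.7% |
| Depression, 50% v 30%, m = 25 | 94% (Sample size, d) | 97.2% | 96.0% | 94.2% |

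Among these variants, only a = 2 matches the 74% and the 94%.

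**Step 2: closed form for the test, strata without effect.** With equal cluster sizes, the uncorrected robust error is √((24 − p)/24) times the unbiased one, where p is the number of facility-level parameters. The rejection rate under the null is P(|t| > 1.96 × √((24 − p)/24)) on 24 − p degrees of freedom.

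- p = 2 (intercept and arm): 1.96 × √(22/24) = 1.877; P(|t22| > 1.877) = **7.4%**. With a 24/23 variance multiplier it is 6.8%. With a t22 reference and no multiplier it is 6.0%.
- p = 7 (five stratum terms added): 1.96 × √(17/24) = 1.650; P(|t17| > 1.650) = **11.7%**. With a t17 reference it is 9.4%.

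**Step 3: simulated logistic GEE under the null.** 8,000 trials per row, Monte Carlo SE about 0.25 points at 5%. Total k is held at 0.2 while the share of between-facility variance due to strata varies. The last column scales the variance by 24/(24 − q) and uses t on 24 − q degrees of freedom, with q = 2, or 7 with strata.

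| Strata in model | Share due to strata | Uncorrected, z | 24/23, z | Uncorrected, t | Corrected, t |
|---|---|---|---|---|---|
| No (as written) | 0% | 6.8% | 6.5% | 5.5% | 4.6% |
| No | 10% | 6.1% | 5.6% | 4.8% | 4.0% |
| No | 20% | 5.6% | 5.1% | 4.4% | 3.6% |
| No | 30% | 4.4% | 4.1% | 3.5% | 2.9% |
| No | 50% | 3.3% | 3.0% | 2.6% | 2.1% |
| Yes | 0% | 11.1% | 10.2% | 8.8% | 4.9% |
| Yes | 30% | 11.4% | 10.6% | 8.9% | 4.7% |

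Unequal facility sizes (coefficient of variation 0.4) give 7.6% for the first row under z, and 12.1% with strata in the model. A separate cluster-mean simulation (200,000 trials, normal approximation, uncorrected z, strata omitted) gave 7.4%, 6.5%, 5.7%, 5.1%, 4.8% and 3.3% at shares of 0, 10, 20, 25, 30 and 50%. The crossing point is therefore near 25%.

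Only the rows with strata in the model, combined with the correction, stay close to 5% whatever the strata explain.

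**The case against.** The strongest reply is that the article says only that the standard errors are robust. It does not say that they are uncorrected or that a normal reference applies. The sandwich variant and the reference distribution are details that an analysis plan, not shown here, may settle. This stands in part: the error rates above are conditional on the usual uncorrected form. But the article does commit to a variance method and to a covariate set for the primary model, and the covariate set leaves out the design strata. As a stated choice for 24 facilities, that is weak.

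Three stronger readings are tempting, and the documents do not support them.

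- A reader might infer that the true type I error is 7–8% and the intervals certainly too narrow. That needs a normal reference, no finite-cluster multiplier and strata that explain nothing. The protocol itself expects stratification to lower the between-facility variation, and with strata omitted the rate can fall below 5%.
- A reader might quote 12% as the error of the planned test. That figure belongs to a stratum-adjusted model that the article does not specify.
- A reader might infer from the two-cluster allowance that planning and analysis contradict each other. The allowance is a back-calculation, not a statement in the text, and it does not show that the analysis will ignore the small number of facilities.

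A sector-specific comparison of six against six facilities ("Phase 1 involves 12 public facilities (Primary Health Centres or PHCs), 6 of which have been chosen at random") would be more exposed, but the article specifies no such test.

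**Conclusion.** The point holds in a conditional form. If the named method is run as the usual uncorrected sandwich with a normal reference and k = 0.2, the two-sided error is about 6–7.5% when strata explain little of the between-facility variance. It is about 3–5% when they explain roughly 25–50% of it. A t reference alone narrows the upper end to about 5.4–6.1%. Adding strata without a correction gives about 9–12%. A correction without strata makes the test conservative, about 2–3.6% when strata explain 20–50%.

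The fault is thus a lack of control, not proven inflation. The result rests on the assumed six equal strata, exchangeable correlation and two-sided testing. It bears on the primary test and is cheap to mend, but the departures from 5% are modest and of uncertain sign, so the severity is moderate.

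**What to change.** State both elements together for all facility-randomised comparisons:

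1. Include the randomisation strata in the GEE, alongside baseline mental health score.
2. Use a small-sample-corrected covariance (Kauermann-Carroll, Mancl-DeRouen or Fay-Graubard) with a t reference on facility-level degrees of freedom, about 24 − 7 = 17 if there are six strata.

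An acceptable alternative is a stratified cluster-level analysis of facility proportions adjusted for baseline score.

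The change takes a sentence or two in the plan. The cost is somewhat wider intervals. If strata explain nothing, the half-width multiplier goes from 1.877 (uncorrected z, no strata) to 2.110 (t17), a ratio of 2.110/1.877 = 1.12. If strata do explain variation, adjusting for them recovers some of that. The stated 74% and 94% already reproduce with two clusters per arm deducted, so an allowance for few clusters of this kind is consistent with the published powers.
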